### Data analysis

Remission will be determined separately at post-treatment and follow-up. The primary outcome analysis will be based upon intent-to-treat. In those cases in which there are missing post-treatment or follow-up data, the pre-treatment observation will be carried forward to characterise that participant’s response [58]. Groups will be compared on remission at post-treatment and follow-up using two-tailed Fisher’s Exact test with *alpha* set to .05. The secondary outcome category is the proportion of participants partially remitted. CFT and PFT will be compared at post-treatment and follow-up using Fisher’s Exact test.

A secondary analysis will be performed using a mixed effects linear regression model [59] to compare CFT and PFT participants on eating pathology, depression and self-esteem at mid-treatment (week 12), end-of-treatment (week 24), 6-month follow-up, and 12-month follow-up controlling for pre-treatment levels. Analyses will be performed on log-transformed variables for behavioural frequencies to satisfy the assumptions for the linear model. Random regression models allow for the inclusion of individuals with missing data. Consequently, no data imputation will be performed. Comparisons between groups will be based upon the main effect for group with a two-tailed alpha of .05. *Post hoc* comparisons between groups at specific time-points will be based upon a two-tailed Bonferroni corrected *Post hoc* comparisons between groups at specific time-points will be based upon a two-tailed Bonferroni corrected *alpha* of .0125 (.05/4).

Moderation analyses will be performed using logistic regression analyses, with models using main effects for treatment, moderator, and treatment-by-moderator analyses to predict remission at post-treatment and follow-up assessments. Bootstrap mediation analyses with bias-corrected confidence intervals will be performed using the *PROCESS* macro developed by Hayes [60].

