### Inclusion criteria

Participants are eligible to participate if they are aged between 12 to 18 years, meet DSM-IV criteria for AN (excluding the amenorrhea criterion) or EDNOS-AN [16], are sufficiently medically stable for outpatient treatment, and are living with at least one parent or guardian who can read and speak English to at least a sixth-grade level. DSM-IV criteria were applied as the trial commenced prior to publication of the DSM-5 [1]. In anticipation of the DSM-5 criteria, however, the amenorrhea criterion was excluded and, in the absence of explicit acknowledgement of fear of weight gain or becoming fat, persistent behaviours that interfere with weight gain are considered diagnostic. Weight thresholds are ≤85% EBW for AN and 85-90% EBW for EDNOS-AN. For adolescents at or above the 75^th^ percentile for height, the weight threshold was set higher (≤95% EBW). EBW is calculated from median body mass index for age and gender using the Centers for Disease Control charts [17]. Medical stability is determined by a paediatrician or nurse according to a standard protocol that was informed by published guidelines [18].

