### Primary outcome

The primary outcome is full remission, defined as ≥ 95% EBW and an EDE Global score within one standard deviation of community norms.

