### Secondary outcomes

The secondary outcomes are partial remission (defined as ≥ 85% EBW) and changes in eating pathology (EDE subscales and behaviour frequency scores), depressive symptoms (CDI) and self-esteem (RSE).

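### Carrying baseline forward counts missing participants enrolled at 85% EBW or more as partially remitted, and sets aside data observed after baseline

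*Protocol article*

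**What the plan says.** The Data analysis section of the protocol article judges remission separately at post-treatment and at follow-up. It says "The primary outcome analysis will be based upon intent-to-treat" and sets this rule for absent values: "In those cases in which there are missing post-treatment or follow-up data, the pre-treatment observation will be carried forward". The same paragraph then compares full and partial remission between arms with Fisher's exact test and gives no separate missing-data rule for partial remission.

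The definitions and entry limits that matter are:

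- Full remission is defined in the section on the primary endpoint: "The primary outcome is full remission, defined as ≥ 95% EBW and an EDE Global score within one standard deviation of community norms".
- The weaker criterion, on weight alone, is in the section on secondary endpoints: "partial remission (defined as ≥ 85% EBW".
- Entry weights are in the Inclusion criteria section: "Weight thresholds are ≤85% EBW for AN and 85-90% EBW for EDNOS-AN". Tall participants (height at or above the 75th percentile) have another limit: "the weight threshold was set higher (≤95% EBW".

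For the continuous outcomes, the next paragraph of Data analysis uses a mixed model without imputation, on the ground that "Random regression models allow for the inclusion of individuals with missing data".

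Table 1 (Measures) schedules weight at every session, at weeks 4, 12 and 24 and at both follow-ups. The EDE is scheduled at baseline, weeks 12 and 24 and both follow-ups.

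**The concern.** One rule is applied to two thresholds that stand differently to the entry range. The full-remission threshold lies at or above every permitted entry weight, so a carried-forward baseline is a failure. The partial-remission threshold lies inside the entry range, so a carried-forward baseline can be a success for someone about whom nothing is known after enrolment. Both outcomes are named in hypothesis 1.

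The rule also looks back only to baseline. A participant seen in full remission at week 24 and at 6 months, but absent at 12 months, returns to the pre-treatment state for the 12-month comparison. The trial will by then hold much better information on that person.

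At stake are the credibility of the partial-remission rates, some power on the primary outcome and, if dropout differs between arms, the validity of the comparison. Unequal dropout cannot be ruled out: the Background and Discussion describe practical difficulty in attending conjoint sessions. The protocol reports no imbalance, however.

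**Working it through.** **Planned figure.** Participants section: 45 per group with 10% dropout. 45 / (1 - 0.10) = 50 per group, which reproduces the stated enrolment.

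**Classification of a participant with missing data under the rule**

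| Entry weight | Full remission | Partial remission |
|---|---|---|
| below 85% EBW | no | no |
| 85% to below 95% EBW | no | yes |
| exactly 95% EBW (tall only) | only if baseline EDE Global is also in the normal range | yes |

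The last row is close to empty, so for full remission the rule is in practice missing = not remitted.

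**Partial remission scored without outcome data.** Let q be the share enrolled at 85% EBW or more and d the share missing, with q taken to be the same among dropouts. The expected count per arm is 50 × q × d. The documents do not give q, so 10-50% is an assumption. At d = 10%:

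- q = 10%: 50 × 0.10 × 0.10 = 0.5 participants (1 point of the arm's rate)
- q = 30%: 50 × 0.30 × 0.10 = 1.5 (3 points)
- q = 50%: 50 × 0.50 × 0.10 = 2.5 (5 points)

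These are counts of participants so classified. They are not estimates of bias.

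**Effect on the arm comparison.** If the true rate is π in both arms and dropouts would have had the same rate, the expected rate in an arm is (1 - d)π + d·c. Here c is the carried-forward rate: about 0 for full remission and q for partial. With missing shares d1 and d2, the spurious difference (arm 1 minus arm 2) is (d1 - d2)(c - π). It is zero when d1 = d2 or when c = π.

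*Full remission*, π = 50% (the Discussion's approximate figure for CFT, used for both arms), c = 0, exact two-sided Fisher test at 50 per arm:

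| Missing (assumed) | Expected rates | Spurious difference | Rejection rate |
|---|---|---|---|
| none | 50% v 50% | 0 | 3.5% |
| 10% v 10% | 45% v 45% | 0 | 3.4% |
| 10% v 20% | 45% v 40% | 5 points | 5.6% |
| 5% v 20% | 47.5% v 40% | 7.5 points | 8.8% |

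Equal dropout still dilutes a real effect. At 10% missing, the planned 27-point difference becomes 0.9 × 27 = 24.3 points. Taking 50% v 77% as an example (the protocol states no base rate), this is 45% v 69.3%. Exact Fisher power at 50 per arm is then 63.8%, against 70.8% with 45 observed per arm at 50% v 77%.

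*Partial remission*, 5% v 20% missing, q = 30%. Everyone fully remitted also has at least 85% EBW, so if full remission is 50%, π is at least 50%. At π = 50%:

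- 0.95 × 0.50 + 0.05 × 0.30 = 49.0%
- 0.80 × 0.50 + 0.20 × 0.30 = 46.0%

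The 3-point gap favours the arm with less missing data, the same direction as for full remission.

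**The case against.** A conservative responder rule for a binary intent-to-treat outcome is a recognised choice, and using a likelihood model for different, continuous outcomes does not in itself contradict it. If dropouts mostly do not remit, missing = not remitted is near the truth, and imputation under missing-at-random could be the more biased option. The protocol plans for 10% dropout and gives no sign that it will differ by arm. The 5.6% and 8.8% figures come from assumed imbalances. All of this stands for full remission, and it is why replacing the primary rule is a matter of judgement.

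The carry-forward sentence directly follows the one on the primary analysis, so its reach to partial remission is a reading. It is the natural one: the sentence speaks generally of missing post-treatment or follow-up data, the paragraph covers both outcomes, and no other rule is offered.

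A reader might infer that the rule pushes the two outcomes in opposite directions. The documents do not support that. By the formula above, it happens only if true partial remission is below the share enrolled at 85% EBW or more. A reader might also infer that missing means success for partial remission across the board. It does so only for those enrolled at or above the threshold; anyone enrolled below 85% EBW is a failure on both outcomes.

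**Conclusion.** The point holds in limited form. As written, the rule credits partial remission to participants with no outcome data whenever they entered at 85% EBW or more. That is about 0.5 to 2.5 of 50 per arm at 10% missing, on an assumed entry share of 10-50%. It also leaves later observed weights and EDE scores unused in the remission analyses.

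Bias in the arm comparison is conditional. It requires unequal dropout, and dropouts whose true remission rate differs from the carried-forward value. Under the assumed 5% v 20% with 50% true full remission, rejection rises from 3.5% to 8.8%. With equal 10% dropout there is no false difference, only attenuation of a true one.

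Separately, the overlap between the entry range and the 85% threshold means some participants meet partial remission at enrolment even with complete follow-up. No missing-data method removes that.

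**What to change.** 1. State the missing-data rule for partial remission explicitly: a baseline value of 85% EBW or more is never carried forward as partial remission, and missing is scored as not partially remitted.
2. Add a pre-specified analysis of full and partial remission that multiply imputes % EBW and EDE Global within arm at week 24, 6 months and 12 months, then derives both outcomes. The imputation model should use baseline, week-4 and week-12 data, session weights and any other observed assessment. Make it either the primary analysis or a named sensitivity analysis beside missing = not remitted.
3. Report, by arm, how many participants already have at least 85% EBW at baseline, so that partial-remission rates can be read against that starting level.

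The cost is analysis wording and some programming. The data are already scheduled for collection and trial conduct does not change. The imputation relies on missing-at-random, which the plan's mixed models already assume. Keeping missing = not remitted alongside it shows how far the result depends on that assumption.

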**Methods/Design:**

This randomised controlled trial will recruit 100 adolescents aged 12–18 years with DSM-IV anorexia nervosa or eating disorder not otherwise specified (anorexia nervosa type). The trial commenced in 2010 and is expected to be completed in 2015. Participants are recruited from the Royal Children’s Hospital Eating Disorders Program, Melbourne, Australia. Following a multidisciplinary intake assessment, eligible families who provide written informed consent are randomly allocated to either parent-focused treatment or conjoint family-based treatment. In parent-focused treatment, the adolescent sees a clinical nurse consultant and the parents see a trained mental health clinician. In conjoint family-based treatment, the whole family attends sessions with the mental health clinician. Both groups receive 18 treatment sessions over 6 months and regular medical monitoring by a paediatrician. The primary outcome is remission at end of treatment and 6 and 12 month follow up, with remission defined as being ≥ 95% expected body weight and having an eating disorder symptom score within one standard deviation of community norms. The secondary outcomes include partial remission and changes in eating pathology, depressive symptoms and self-esteem. Moderating and mediating factors will also be explored.

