### Aims and hypotheses

The aims of this study are to:

1. Examine the relative benefits of PFT compared to CFT in a randomised controlled trial with a cohort of outpatients with AN and EDNOS- Anorexia Nervosa type (EDNOS-AN);

2. Explore predictors and moderators of treatment response; and

3. Explore mediators of treatment response.

It is hypothesised that:

1. PFT will be more effective than CFT as indicated by more participants achieving full remission and partial remission after 6 months of treatment and at 6 and 12 months follow-up;

2. Adolescents with parents who are highly critical and are assigned to PFT will have better outcomes compared to adolescents with parents who are highly critical and are assigned to CFT;

3. Regardless of treatment assignment, outcomes will be poorer for adolescents with co-morbid psychiatric illness, high levels of obsessionality, features of personality disturbance, parent psychopathology, high levels of parental criticism, poor therapeutic relationship, and/or low expectation for treatment effectiveness. These factors will also be explored as potential moderators of outcomes with respect to treatment assignment;

4. Treatment response will be mediated by reduced dietary restraint and depressive symptomatology, and increased self-esteem, parent efficacy and family functioning.

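### Full remission is primary at three time points, each tested at .05 with no deciding visit, order or correction; if any one visit can count as success, the false-positive chance is roughly two to three times that of one test

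*Protocol article*

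**What the plan says.** The time points come from three places in the protocol article.

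- The abstract (Methods/Design) states: "The primary outcome is remission at end of treatment and 6 and 12 month follow up".
- Hypothesis 1, under Aims and hypotheses, expects PFT to do better, shown by "more participants achieving full remission and partial remission after 6 months of treatment and at 6 and 12 months follow-up".
- The Primary outcome section gives the definition but no visit: "The primary outcome is full remission, defined as ≥ 95% EBW and an EDE Global score within one standard deviation of community norms".

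Data analysis then fixes the test. "Remission will be determined separately at post-treatment and follow-up", and "Groups will be compared on remission at post-treatment and follow-up using two-tailed Fisher’s Exact test", with alpha at .05. The article does not say which visit decides, whether the visits are tested in order, or whether all must succeed.

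Two other statements bear on this. The Participants section sizes the trial for one comparison of remitted with non-remitted patients: 80% power, two-tailed .05, a 27-point difference, 45 per group, and 50 after 10% dropout. Data analysis also sets a Bonferroni limit of .0125 (.05/4) for post hoc comparisons at single time points, but only within the mixed model for the secondary scores.

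**The concern.** Three separate tests of the primary outcome, each at .05, offer three chances of a false positive. As written, a significant difference at one visit with nothing at the other two could be reported as success on the primary outcome. If the visits disagree, nothing in the text settles which one answers the question.

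This is more than detail left to a fuller document. The article itself chooses the test, its sidedness and its alpha for the primary outcome. In the same section it corrects for repeated visits on secondary scores, so the more important outcome has the weaker protection. The Discussion says that the trial will show whether PFT is a more efficacious alternative to CFT, and that claim rests on this rule.

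**Working it through.** **1. The plan's own sample size is for one test.** The Participants section states no control remission rate. Taking 50% from the Discussion as an assumption, and 77% with PFT:

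n = (1.960 + 0.842)² × [.50 × .50 + .77 × .23] / .27² = 7.849 × .4271 / .0729 ≈ 46.0 per group.

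This is close to the stated 45, and 45/.90 = 50. The stated size is therefore reproduced with the whole .05 spent on one comparison. (A pooled-variance formula gives 49.)

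**2. Three nominal 5% tests.** If independent, 1 − .95³ = .143, or 2.85 times one test. With equal correlation between the three test statistics, simulation gives 12.5% at .5, 11.0% at .7, 9.8% at .8 and 8.4% at .9. The ratios are 2.5, 2.2, 2.0 and 1.7.

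**3. The test actually planned.** Fisher's exact test is conservative. With 50 per arm and equal true remission in both arms, one two-tailed test at .05 rejects in about 3.1% of trials at 30% remission and 3.5% at 50%. If the three visits were independent, 1 − .969³ = 9.0% and 1 − .965³ = 10.1%.

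For correlated visits, remission was simulated by cutting correlated normal variables at the remission rate (100,000 trials per setting). The latent correlation is that of the underlying normals.

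| Remission, both arms | Latent correlation | One test | Any of three | Ratio | Any of three, favouring PFT |
|---|---|---|---|---|---|
| 30% | 0 | 3.1% | 9.0% | 2.9 | 4.6% |
| 30% | .5 | 3.0% | 8.4% | 2.8 | 4.2% |
| 30% | .9 | 3.1% | 6.9% | 2.3 | 3.4% |
| 50% | 0 | 3.5% | 10.1% | 2.9 | 5.2% |
| 50% | .5 | 3.6% | 9.8% | 2.7 | 5.0% |
| 50% | .9 | 3.5% | 7.6% | 2.2 | 3.8% |

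One test falsely favours PFT in about half of its rejections, so about 1.5% to 1.9% of trials.

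**4. Scale of the correlation.** A latent correlation of .9 at 50% remission is a correlation of (2/π) × arcsin(.9) = .71 between the yes/no outcomes themselves. If the yes/no outcomes correlated at .9, any-of-three would fall to 5.3% to 6.0%, a ratio of about 1.7.

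**5. Cost of a plain correction.** Bonferroni at .05/3 = .0167 gives 1 − (1 − .0167)³ = 4.9% for independent nominal tests. For 50% against 77% it would need 66 per group instead of 49 (pooled formula). Power with 45 per group would fall from about 77% to 61%.

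**The case against.** **All three visits might be required.** Hypothesis 1 joins the visits with the word and. If PFT had to win at every one, there would be no inflation. The article does not say so, and that rule would cost power. The text is therefore open, and the figures here apply only if one significant visit is enough.

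**The inflation is smaller than simple arithmetic suggests.** A reader might quote 14.3%. That figure needs independent visits and tests that truly reject 5% of the time. Fisher's test does not, and the same patients are classified at each visit. Carrying the pre-treatment observation forward also makes anyone missing at several visits a repeated non-remitter, which raises the correlation. About half of the false positives would favour CFT. This stands, and is why the Fisher-based and directional figures are the ones to use.

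**Six tests?** A reader might add partial remission at three visits, since hypothesis 1 mentions it. The article labels partial remission secondary, so it does not belong in the error rate of the primary outcome.

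**Does the sample size point to week 24?** A reader might infer that end of treatment is the intended visit. The Participants section supports a single comparison but names no visit.

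**The article is condensed, and the tests are openly listed.** A testing hierarchy may sit in a fuller document, and readers can count the tests. But the article states an alpha for each primary comparison, and that statement needs a deciding rule beside it.

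**Conclusion.** The point holds. The plan makes full remission primary at three visits, tests each at .05, and gives no rule for deciding between them. If any one visit suffices, the chance of a false positive is roughly two to three times that of one test: about 7% to 10% two-sided against 3.0% to 3.6%, and roughly 3.4% to 5% for a false claim in favour of PFT against about 1.5% to 1.9%.

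The assumptions are 50 per arm, 30% to 50% true remission in both arms, and a latent correlation between visits of 0 to .9. The article fixes neither the remission rate nor the correlation. Stronger correlation would lower the ratio to below two. The absence of a rule for conflicting visits does not depend on any of these figures.

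**What to change.** Before the data are complete, and without sight of results by arm, name one deciding visit for full remission and test it at two-tailed .05. End of treatment is one possibility; the sample-size paragraph names none, so the choice is the sponsor's. Test the other two visits in a stated order, each at .05 and only if the preceding test was significant. State the same rule in the abstract, hypothesis 1, Primary outcome and Data analysis, and keep partial remission secondary.

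The cost is a sentence or two. Alpha for the deciding test stays at .05, so no more participants are needed, unlike with Bonferroni. The drawback is that a difference seen only at a later-ordered visit becomes supportive, not confirmatory. If the sponsor means that all three visits must succeed, the article should say so and accept the loss of power.

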### Participants

Participants will be 100 families of adolescents aged between 12 and 18 years inclusive. Eligible participants are identified during triage and intake assessment. Sample size calculation for this study was based upon two controlled trials of FBT [6,8]. It was calculated that for 80% power and a two-tailed significance level of .05, it would be possible to detect an 27% difference between CFT and PFT (dichotomous outcome of remitted versus non-remitted) with a sample size of 45 participants per group. Assuming a dropout rate of 10%, the enrolled sample size requires 50 participants per group.

Treatment groups will be compared on sociodemographic and clinical characteristics at baseline using Fisher’s Exact test for dichotomous variables (e.g., gender, family status), chi-square for categorical variables (e.g., ethnicity, comorbid diagnoses), and independent sample t-tests for continuous measures (e.g., age, % EBW).

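### The four visit-specific comparisons use single-step Bonferroni at .0125. That is valid, but Holm's step-down procedure gives the same error control and locates differences by visit somewhat better

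*Protocol article*

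**What the plan says.** The Data analysis section sets out two layers of testing for the continuous outcomes.

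- **Model.** "A secondary analysis will be performed using a mixed effects linear regression model" for eating pathology, depression and self-esteem. The arms are compared "at mid-treatment (week 12), end-of-treatment (week 24), 6-month follow-up, and 12-month follow-up controlling for pre-treatment levels", so there are four post-baseline assessments.
- **Overall test.** "Comparisons between groups will be based upon the main effect for group with a two-tailed alpha of .05".
- **Visit-specific tests.** These are labelled post hoc: "comparisons between groups at specific time-points will be based upon a two-tailed Bonferroni corrected" alpha of .0125, with .05/4 shown in brackets. The sentence is partly printed twice. That is an editing slip and leaves the rule clear.

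The primary outcome, full remission, lies outside this correction: "Groups will be compared on remission at post-treatment and follow-up using two-tailed Fisher’s Exact test with" alpha at .05.

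**The concern.** Single-step Bonferroni holds every visit to .0125 whatever the other three show. Holm orders the four p-values and compares them in turn with .05/4, .05/3, .05/2 and .05, stopping at the first failure. Its first threshold equals the Bonferroni threshold and the later ones are easier. It can therefore only add rejections, and it needs no assumption about how the visits are correlated.

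At stake is the description of when the treatments differ. If a difference is present at several assessments, for example at end of treatment and both follow-ups, the fixed .0125 will more often miss some of those visits. The trial plans 100 families, so power at a single visit is limited.

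**Working it through.** **1. The plan's own figure.** .05/4 = .0125, and the divisor matches the four named assessments. The four alphas sum to .05. If the tests were independent, the familywise error would be 1 − (1 − .0125)^4 = .0491. Positive correlation lowers it: simulation gives .043 at correlation .5 and .032 at .8. The rule does what it claims.

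**2. Holm thresholds.** .05/4 = .0125, .05/3 = .0167, .05/2 = .025 and .05/1 = .05, applied to the ordered p-values and not to visits in calendar order.

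**3. Inputs for power.** The number of visits (4) and the alpha come from the Data analysis section. The 50 enrolled per arm comes from the Participants section. The rest is assumed: correlation r = .5 between baseline and each visit, rv = .6 between visits, a baseline-adjusted comparison, normal test statistics and complete data.

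- Standard error per visit, in SD units: √(2(1 − r²)/n) = √(2 × .75/50) = .173.
- Residual correlation between visits: (rv − r²)/(1 − r²) = (.6 − .25)/.75 = .467.
- Bonferroni power at one visit for 0.5 SD: the critical value at two-sided .0125 is 2.498, so Φ(0.5/.1732 − 2.498) = Φ(0.389) = 65%.

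**4. Bonferroni against Holm** (simulated sets of four correlated z-statistics; power is averaged over the visits that have an effect):

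| Assumed effect | Bonferroni | Holm | Gain (points) |
|---|---|---|---|
| 0.5 SD at all four visits | 65.1% | 74.2% | about 9 |
| 0.4 SD at all four | 42.6% | 50.4% | about 8 |
| 0.3 SD at all four | – | – | about 4 |
| 0.5 SD at three (none at week 12) | 65.3% | 70.4% | about 5 |
| 0.5 SD at two | – | – | about 2 |
| 0.5 SD at one | 65% | 65% | 0 |

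The chance of detecting every true effect rises from 33.7% to 55.9% with 0.5 SD at all four visits, and from 40.1% to 51.2% with 0.5 SD at three. With no effect anywhere, familywise error is 4.4% for both. The chance of at least one rejection is identical in every scenario, because the first Holm step is the Bonferroni test.

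**5. A second set-up.** The sample size section works "with a sample size of 45 participants per group". With 45 per arm, an assumed 0.6 SD and correlation .5 between the test statistics, power per visit is 63.6% against 72.6% when all four visits have an effect, and all four are detected in 33% against 55%. With one affected visit it is 63.5% for both. No run had a Bonferroni rejection that Holm missed. When some effects were real, Holm's familywise error was at most .045.

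**6. The main-effect test under the assumptions of step 3.** Treat the main effect for group as the mean of the four visit contrasts. Its standard error is .1732 × √((1 + 3 × .467)/4) = .1732 × .775 = .134. Power at two-sided .05 is then:

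- 0.5 SD at all four visits: Φ(0.5/.1342 − 1.960) = Φ(1.77) = 96%.
- 0.4 SD at all four: Φ(0.4/.1342 − 1.960) = Φ(1.02) = 85%.
- 0.5 SD at three visits (mean 0.375): Φ(0.375/.1342 − 1.960) = Φ(0.83) = 80%.

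**The case against.** The strongest reply is that nothing here is wrong. Bonferroni at .0125 is prespecified, correctly computed and matched to the four assessments, and choosing it over another valid procedure is a preference. That stands as far as validity goes: the point is one of efficiency.

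Three stronger readings are tempting, and the article does not support them.

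- **That the trial would miss a sustained effect.** A reader might infer this from the per-visit figures. But the main effect for group is tested at .05 without this adjustment. By step 6 it has 80% to 96% power in the scenarios where Holm gains 5 to 9 points.
- **That the gain is always that large.** It needs moderate effects at three or four visits. It falls to about 4 points at 0.3 SD, about 2 with two affected visits and none with one. If no p-value reaches .0125, Holm adds nothing.
- **That Bonferroni gives up power for nothing.** It supplies matching 98.75% intervals at each visit (100% − 1.25%), which is useful for describing differences. Holm has no equally simple counterpart.

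The consequence is also limited. The primary remission comparison and the sample size do not depend on this rule. Neither method addresses multiplicity across outcomes, because each covers only the four visits of one outcome.

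What remains is that, for reject or do-not-reject decisions at the visits, Holm is at least as good in every case and needs no extra assumption.

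**Conclusion.** The point holds as an optional, low-priority improvement and not as an error. Holm would keep strong familywise control at .05 and add between 0 and about 9 points of per-visit power across the scenarios examined, depending on the size of the effect and how many visits show it. These figures rest on assumed effect sizes and correlations, since the article states none for these outcomes. That Holm rejects everything Bonferroni rejects, and controls the same error under any dependence, rests on no such assumption. The benefit is confined to showing at which assessments PFT and CFT differ.

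**What to change.** Before comparative data are seen, replace the .0125 rule with wording such as: *Within each outcome, the comparisons at the four time points will be tested by the Holm step-down procedure, with ordered p-values compared with .05/4, .05/3, .05/2 and .05, stopping at the first failure; Holm-adjusted p-values will be reported.* Remove the duplicated sentence fragment in the same edit.

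The cost is one line, with no loss of error control and no change to the sample size or the primary analysis. The downside is that simple simultaneous confidence intervals will not match the Holm decisions exactly. The 98.75% Bonferroni intervals can still be reported descriptively, with a note saying so. If exact agreement between intervals and tests matters more to the trial team than the added power, keeping Bonferroni is defensible.
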